In a pilot study evaluating the implementation of our own transition program, we showed that patients with complex CHD, poor disease knowledge, risk behaviours, and lower age, were more likely to join this transition program [6]. However, these preliminary results come from a non-randomized controlled study. Therefore, the impact of this transition program needs to be determined with a higher level of evidence.

In the TRANSITION-CHD trial, we aim to assess the impact of a non-selective structured education transition program on HRQoL of adolescents and young adults with CHD, through a regional multicentre randomised trial. We also intend to perform a qualitative phenomenological study to explore how these young patients experience the TRANSITION-CHD program and identify key factors for success or failure.

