## Methods

### Study design

The TRANSITION-CHD trial is an open label prospective, multicentre, randomised, controlled, parallel arm study. Patients will be followed for 12 months with an expected recruitment time period of 24 months.

Once the informed consent will be given, participants will be randomly allocated in a 1:1 ratio to either intervention (e.g. transition education program) or control group arms. In the control group, patients will have a regular non-modified follow-up with no formalized transition education program during the 12-month study period. However, they will be offered to participate in the transition therapeutic education program, once the 12-month study period is over (Fig. 1).

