### Statistical analysis

All included subjects will be considered in the description of the population. An intention-to-treat analysis will be used, and each randomized subject will be analysed in his/her treatment arm. A per-protocol analysis, including all randomized subjects with a valid primary efficacy measurement and with no important protocol deviation (patients who have successfully completed the transition program) that could affect the evaluation of the main outcome, will also be carried out for parameters to assess the impact of the program when compliance is good (> 80% participation in sessions).

A description of the baseline characteristics of each group will be made by giving the frequencies of the different categories for the qualitative variables and the mean with standard deviation or median with interquartile range for continuous variables. In case of non-comparability of the groups, an adjustment or stratification (in case of interaction) on the potential confounding factors will be considered in a sensitivity analysis.

The change in the self-reported HRQoL total score, as well as the changes of the 2 summary and the 4 dimensions scores, will be compared between the two groups using student test or Man-Whitney test, according to the distributions. The effect size will be calculated using Cohen’s d and its 95% confidence limits.

The statistical significance will be set at 0.05 and analyses will be performed using Statistical Analysis Systems version 9 (SAS Institute, Cary, NC, USA).

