## Discussion

In the continuity of our clinical research program on HRQoL in patients with CHD [6, 14, 30–32, 34], we expect to observe an improvement of HRQoL in patients undergoing the transition education program. Patient-reported outcomes (PRO) have been increasingly used in clinical research [35], therefore, using HRQoL as a primary outcome in the TRANSITION-CHD trial seems particularly adapted to such a therapeutic education program. Indeed, as defined by the World Health Organization, “therapeutic education should try to give and maintain the necessary competences to handle chronic disease with the objective of improving patient HRQoL”.

Currently, the level of evidence of research in therapeutic education needs to be improved, despite all methodological constraints and biases inherent to qualitative research: various qualitative outcomes, heterogeneous educational content, ethical issues related to randomisation, program based on voluntary patient participation, etc. [36]. The TRANSITION-CHD trial will use several quantitative instruments assessing various aspects of the patient well-being: self and proxy-reported HRQoL, anxiety, depression, level of autonomy and disease knowledge. In order to limit the level of content heterogeneity, this education program is based on a single and joint structure between all tertiary care CHD centres from the same region [6]. Therefore, ethical issues have been considered in the study design, and patients randomised in the control group will be offered to participate in the transition program, without any additional cost, after the 12-month study period. Since the creation of the program in 2015, all paediatric and adult congenital cardiologists from the regional M3C network have been particularly motivated to enrol their patients and participate themselves in the education sessions. Active support from all patient organisations has played an important role in promoting the program, as shown in several videos dedicated to young patients with CHD (https://www.youtube.com/watch?v=OJ67oIm0Wv8).

Promotion of physical activity is a major educational objective of the transition program. Indeed, exercise capacity in the CHD population may be impaired and many adolescents with a sedentary lifestyle are trapped in the vicious circle of physical deconditioning [15, 24, 31, 34]. Similar therapeutic education messages focusing of sports participation have been integrated into cardiac rehabilitation programs [15].

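### The per-protocol analysis selects on programme completion in one arm only, so it does not in general estimate the programme's effect under good compliance

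*Protocol article*

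**What the plan says.** The Statistical analysis section of the protocol article puts intention-to-treat first: "each randomized subject will be analysed in his/her treatment arm". It then adds a per-protocol analysis. Subjects in either arm need an evaluable primary outcome, and must meet a further condition, worded as "no important protocol deviation (patients who have successfully completed the transition program) that could affect the evaluation of the main outcome". The stated aim is "to assess the impact of the program when compliance is good", where good compliance means taking part in more than 80% of sessions.

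Under Study design, controls are told apart by having no programme: "patients will have a regular non-modified follow-up with no formalized transition education program during the 12-month study period". They are offered it only after the 12 months are over.

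The only provision for confounding in the Statistical analysis section is an adjustment or stratification to be considered, as a sensitivity analysis, if the groups turn out not to be comparable. It is not tied to the per-protocol set. The Discussion lists "program based on voluntary patient participation" among the constraints of this kind of research.

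**The concern.** Completion is decided after randomisation, and here it can be observed in one arm only. Would-be non-completers are removed from the intervention arm, while their counterparts stay in the control arm because nobody can identify them. The two groups are then no longer alike by design. If staying the course goes with a better or worse change in PedsQL score for reasons unrelated to the programme, that difference is counted as programme effect.

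Such an association is plausible. Under Intervention, the programme ends with a transfer visit about 6 months after the group day, so intervention patients must stay engaged well into follow-up to qualify. The trial is also open label with a self-reported outcome.

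What is at stake is how a secondary result is read. The article gives this contrast a causal meaning in advance, as the programme's impact under good compliance, and the comparison as defined does not generally have that meaning.

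**Working it through.** **The plan's own figure.** The article gives no figure for the per-protocol analysis. Its only related number is the sample size of 100 per arm. From the stated inputs (difference 7, SD 13.5, two-sided 5%, 80% power), n = 2 × (1.960 + 0.842)² × 13.5² / 7² = 58.4, so 59 per arm, and 59 / 0.8 = 73.75, so 74 with 20% loss. The stated 100 is not reproduced at 80% power; 90% power gives 79, or 99 with loss. That is a separate matter and does not affect this point.

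**Inputs from the article.** SD 13.5 (taken as the SD of the change score), target 7 points, 100 per arm, 20% loss. This leaves 100 × 0.8 = 80 evaluable per arm.

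**Inputs that are assumptions.** c, the share of the intervention arm that completes, from 0.5 to 0.9. D, the mean change of would-be completers minus that of would-be non-completers when neither gets the programme, from 0 to 7 points.

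**Bias.** Let m1 and m0 be the mean changes of would-be completers and non-completers without the programme, so D = m1 − m0. Randomisation gives both arms the same mix.

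- Intervention completers, no programme effect: m1.
- Evaluable controls: c × m1 + (1 − c) × m0.
- Difference: (1 − c) × (m1 − m0) = (1 − c) × D.

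**Type I error.** SE = 13.5 × √(1/80 + 1/(80c)). At c = 0.7 there are 56 completers, so SE = 13.5 × √(0.01250 + 0.01786) = 2.35. With D = 5 the bias is 0.3 × 5 = 1.5 points, or 1.5 / 2.35 = 0.64 SE. The rejection rate is 1 − Φ(1.96 − 0.64) + Φ(−1.96 − 0.64) = 9.8%.

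Bias in points, with type I error at a nominal 5%:

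| c | D = 0 | D = 3 | D = 5 | D = 7 |
|---|---|---|---|---|
| 0.9 | 0 (5.0%) | 0.3 (5.2%) | 0.5 (5.6%) | 0.7 (6.2%) |
| 0.8 | 0 (5.0%) | 0.6 (5.8%) | 1.0 (7.3%) | 1.4 (9.5%) |
| 0.7 | 0 (5.0%) | 0.9 (6.7%) | 1.5 (9.8%) | 2.1 (14.5%) |
| 0.6 | 0 (5.0%) | 1.2 (7.8%) | 2.0 (12.8%) | 2.8 (20.6%) |
| 0.5 | 0 (5.0%) | 1.5 (8.8%) | 2.5 (16.0%) | 3.5 (26.8%) |

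A negative D gives the same sizes with the sign reversed.

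**Check by simulation.** In 4,000 trials with c = 0.7, D = 5 and no programme effect, the mean per-protocol difference was 1.52 points and the rejection rate 9.6%. In the same trials, the intention-to-treat difference divided by the share completing averaged 0.03 points.

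**Precision of the alternative.** The intention-to-treat SE is 13.5 × √(2/80) = 2.13. Divided by 0.7 it is 3.05, against 2.35 for the per-protocol contrast.

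**The case against.** The strongest reply is that this analysis is supplementary. Intention-to-treat comes first, no decision rule rests on the per-protocol result, and any per-protocol set for a programme with an untreated control arm has this feature. The article may also leave deviation criteria for controls to a fuller document. This stands as a limit on severity. It does not remove the problem, because the article itself states the selection rule, the threshold and the intended meaning, and these do not fit together.

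Size is a second reply. c and D are assumptions, D = 7 equals the whole target effect, and even the largest bias in the table is below the 5 points that the Sample size section treats as irrelevant. This is fair. But the bias adds to any real effect, and it raises the false-positive rate well before it reaches 5 points.

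A reader might also infer more than the article supports:

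- *That the rule empties the control arm, or that all controls are used.* The first is a strained reading of the parenthesis. Against the second, the measurement and no-deviation conditions apply to controls too.
- *That the pilot shows completers to be different.* The Background reports that "patients with complex CHD, poor disease knowledge, risk behaviours, and lower age, were more likely to join this transition program". That concerns joining a non-randomised programme. Here consent precedes randomisation, so selection at joining affects both arms alike. The support for selective completion is indirect at most.
- *That the bias favours the programme.* Nothing in the article fixes the sign of D, and the pilot's joiners were not an obviously favourable group.
- *That more than 80% of sessions means all three parts.* Sessions are not defined. With three parts, 2 of 3 (67%) fails. If the four parts of the group day count separately there are six components, and 5 of 6 (83%) passes.

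Finally, a complier-average estimate has its own weak point. Suppose, for illustration, that 90% attend the group day and gain 7 points, but only 70% complete everything. Defining compliance as full completion then gives 0.9 × 7 / 0.7 = 9.0, which is 2 points too high. This objection stands and shapes the fix.

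**Conclusion.** The concern holds in a limited form. The per-protocol contrast sets intervention completers against all evaluable, non-deviating controls. It loses the protection of randomisation, and no method for that selection is tied to it. It does not in general estimate the effect under good compliance. It would be too strong to say that it cannot: the bias is zero if completion is unrelated to the change in score (D = 0), and adjustment for whatever predicts both would also remove it.

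Under the assumed ranges the bias is 0 to 3.5 points, that is 0 to 50% of the 7-point target. The middle case of 1.5 points is 21% of the target. The actual size and direction cannot be known from the article. Severity is modest because the main inference rests on intention-to-treat, but the change is worth making before the data are analysed.

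**What to change.** Keep intention-to-treat for inference. For the effect under compliance, specify a complier-average causal effect with randomised arm as the instrument, for example by two-stage regression adjusted for baseline PedsQL score and age stratum. Non-compliance is one-sided by design, since controls have no access to the programme before month 12.

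Define compliance as attending the group day, with full completion as a sensitivity definition. In the illustration above, the group-day definition returns 0.9 × 7 / 0.9 = 7. State a single rule for full completion, say what counts as a session, and say what counts as an important deviation for a control. If completers versus controls is still reported, label it exploratory and drop the claim that it measures impact under good compliance.

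The cost is analysis wording and one additional model. No new patients are needed, and attendance must be recorded anyway to apply the 80% rule. The drawbacks are:

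- a wider confidence interval, because the standard error is roughly divided by the compliance proportion;
- an assumption of no effect in patients classed as non-compliers, which fails, and overstates the effect, if partial attenders benefit;
- the usual assumption about missing outcomes.

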**Fig. 1 Fig1:**
[figure not shown]
Flow chart

Randomisation will be stratified by age group (13–17 years and 18–25 years), centralised, using a secure, web-based randomisation system (Ennov Clinical Software) managed by the Clinical Research Unit of Montpellier University Hospital, independently from the investigators.

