### Main outcome

The main outcome is the change between baseline (M0) and 12-month follow-up (M12) of the PedsQL self-reported HRQoL score. The PedsQL generic HRQoL questionnaire has four multidimensional scales: physical functioning (8 items), emotional functioning (5 items), social functioning (5 items), and school functioning (5 items). The three summary scores are: total scale score (23 items), physical health summary score (8 items) and psychosocial health summary score (15 items). Each item uses a 5-point Likert scale from 0 (never) to 4 (almost always). Items are reversed scored and linearly transformed to a 0–100 scale, higher scores indicating a better HRQoL. Psychometric properties showed reliability, validity and responsiveness to clinical change over time [22]. After translation and cultural adaptation, the psychometric properties of the French version of the PedsQL appeared to be acceptable [23]. Two versions of the PedsQL questionnaire (13–17 and 18–25 years old) will be used for adolescents and young adults, respectively.

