### Sample size

The primary outcome is the change in the self-reported HRQoL score with the PedsQL instrument. In our previous HRQoL cross-sectional studies in patients with CHD [14, 30, 31] as well as in similar studies using patient related outcomes, a difference of less than 5 points seems irrelevant and a difference of more than 10 points is ideal, but rarely obtained in clinical trials [32, 33]. Therefore, we hypothesized to observe an increase in the overall HRQoL score of 7 ± 13.5 points (over 100). With a 80% power, a bilateral alpha risk of 5%, and potentially 20% of loss to follow-up and/or missing data on the primary outcome, we need to include 100 patients in each group.

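### The primary t or Mann-Whitney test on PedsQL change is valid but inefficient: it adjusts for neither baseline score nor age stratum, and it leaves open which effect the p-value tests

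*Protocol article*

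**What the plan says.** Under Main outcome, the protocol article states: "The main outcome is the change between baseline (M0) and 12-month follow-up (M12) of the PedsQL self-reported HRQoL score". Under Statistical analysis, the change in the total score, and in the summary and dimension scores, "will be compared between the two groups using student test or Man-Whitney test, according to the distributions". Cohen's d with 95% limits is to be reported. The section gives no rule for judging the distributions.

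The only covariate adjustment in that section depends on the groups turning out non-comparable at baseline. In that case "an adjustment or stratification (in case of interaction) on the potential confounding factors will be considered in a sensitivity analysis".

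The randomisation paragraph below the flow chart (Methods, Study design) says: "Randomisation will be stratified by age group", the bands being 13–17 and 18–25 years. The instrument also differs between these bands: "Two versions of the PedsQL questionnaire (13–17 and 18–25 years old) will be used for adolescents and young adults, respectively". Neither the stratum nor the baseline score is a covariate in the primary comparison.

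The Sample size section plans on an increase of 7 ± 13.5 points, 80% power, two-sided 5% and 20% loss, with 100 patients per arm.

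**The concern.** Three features of the stated primary analysis give something away.

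- **Baseline.** A change score subtracts the baseline in full, as if the slope of M12 on M0 were 1. When the slope is below 1 this over-corrects. Noise is added, and an arm that starts lower by chance tends to show a larger rise.
- **Age stratum.** Stratified allocation balances age between arms. A test that leaves age out keeps the between-age variation in its error term and does not collect the precision that the stratification bought.
- **Target of the test.** A t test addresses the mean difference, on which the trial is powered and on which Cohen's d rests. Mann-Whitney is a rank comparison. If the data lead to the second, the p-value and the reported effect describe different quantities.

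At stake are the width of the confidence interval for the primary result and a clear statement of what is being tested.

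**Working it through.** **Inputs from the protocol article.** Difference 7, SD 13.5, two-sided alpha 5%, power 80%, loss 20%, 1:1 allocation, 100 per arm. Completers per arm: 100 × 0.8 = 80.

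**The plan's own figure.** n per arm = 2 × [(1.960 + 0.842) × 13.5 / 7]² = 58.4, so 59 evaluable, and 59 / 0.8 gives 74 after loss. The stated 100 per arm does not follow from these inputs. That is a separate matter and does not affect this point. The power figures below use the 80 completers that the stated 100 would leave.

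**Assumptions not in the documents.** Equal variance σ² at M0 and M12, and the M0 to M12 correlation r, shown from 0.3 to 0.9.

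**Variance ratio.** Var(change) = 2σ²(1 − r). ANCOVA residual variance = σ²(1 − r²). The ratio is (1 + r)/2, below 1 for every r below 1.

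**If 13.5 is the SD of the change.** The ANCOVA SD is 13.5 × √((1 + r)/2). Power = Φ(difference / (SD × √(2/80)) − 1.960). The unadjusted SE is 13.5 × √(2/80) = 2.13, so power for 7 points is Φ(7/2.13 − 1.96) = 90.6% (90.3% by the exact t test).

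| Analysis | Variance ratio | SD | Evaluable n per arm, 80% power, 7 points | Power for 7 points, 80 per arm |
|---|---|---|---|---|
| Change score | 1.00 | 13.50 | 59 | 90.6% |
| ANCOVA, r = 0.3 | 0.65 | 10.88 | 38 | 98.2% |
| ANCOVA, r = 0.5 | 0.75 | 11.69 | 44 | 96.6% |
| ANCOVA, r = 0.7 | 0.85 | 12.45 | 50 | 94.5% |
| ANCOVA, r = 0.9 | 0.95 | 13.16 | 56 | 92.0% |

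**If 13.5 is the SD of a single score.** The article cites cross-sectional studies just before the figure and does not say which SD it is. Then SD(change) = 13.5 × √(2(1 − r)) and SD(ANCOVA) = 13.5 × √(1 − r²). Evaluable n per arm for 7 points, change score against ANCOVA: 82 against 54 at r = 0.3, 59 against 44 at r = 0.5, 36 against 30 at r = 0.7. The ratio (1 + r)/2 is the same.

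**Chance baseline imbalance.** Given a baseline difference D between arms, the change comparison is shifted by −(1 − r)D. At r = 0.5 with an SD of change of 13.5, the single-score SD is also 13.5 and the SE of D is 2.13. An imbalance of one SE shifts the observed difference by 0.5 × 2.13 = 1.07 points. Averaged over randomisations the shift is zero.

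**Age stratum (simulation).** With 80 per arm, half in each age band and SD 13.5, the unadjusted t test has type I error 0.050 when mean change does not differ by age. It is 0.048, 0.044 and 0.037 when mean change differs by 3, 5 and 10 points. The test becomes conservative, not liberal.

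**Choice of test (simulation).** With 80 per arm and normal, heavy-tailed or skewed data, choosing by a normality pre-test gives type I error 0.052–0.054. Reporting the smaller of the two p-values would give 0.061–0.080, but the article does not plan that.

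**The case against.** The strongest defence is that nothing here is invalid. Under 1:1 randomisation the change-score difference is unbiased, type I error is near or below 5%, and at the planned 7 points power is already about 90% if 13.5 is the SD of the change. The gain rests on a correlation that the documents do not give. At r = 0.9 it is under two percentage points of power. How the distributions are to be judged may well be set out in an analysis plan that is not shown, and a mean-based effect, Cohen's d, is promised whichever test is used.

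Most of this stands, and it rules out several stronger readings that a reader might infer:

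- *That the analysis ignores baseline.* It does not. The change score subtracts it; what is missing is baseline as a covariate.
- *That the result is biased.* Imbalance shifts the result only conditionally, in a given sample.
- *That the test is picked after the fact to suit the result, or inflates type I error.* The text names the distributions as the criterion, and switching by a normality check does little harm.
- *That the trial depends on ANCOVA for adequate power.* Larger gains can be shown by moving to 5 points: at r = 0.6 with 13.5 as a single-score SD, power goes from about 74% to 83%. But 5 points is the edge of relevance in the Sample size section, not the design target, and that figure uses the other reading of the SD.

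The defence does not meet two points. The article itself states an unadjusted primary test, so this is not something merely left to a later document. An adjustment that depends on observed imbalance and is confined to a sensitivity analysis does not recover the lost precision. Reporting Cohen's d in every case also does not tell the reader what a Mann-Whitney p-value refers to.

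**Conclusion.** The point holds as one of efficiency and clarity, not validity. The stated primary analysis has 1/((1 + r)/2) times the variance of a baseline-adjusted one: 1.54 times at r = 0.3, 1.33 at 0.5, 1.18 at 0.7 and 1.05 at 0.9. This assumes equal M0 and M12 variances. With 13.5 as the SD of the change and 80 completers per arm, power for 7 points would be 92–98% instead of about 90%.

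Leaving out the age stratum costs something only if mean change differs by age, and then makes the test slightly conservative. The open choice between t and Mann-Whitney leaves the target of the p-value undecided. The documents do not support a claim of bias or of an inflated error rate. The change is worth making because it costs almost nothing, not because the planned conclusion would be unsafe without it.

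**What to change.** Replace the primary comparison with one prespecified ANCOVA: M12 PedsQL total score (or the change, which gives the same arm effect once baseline is in the model) on arm, baseline total score and age stratum as randomised (13–17 / 18–25). Report the adjusted mean difference in points with its 95% CI, and give Cohen's d as a supplement. Keep the rank test as a sensitivity analysis only. Name the covariates in advance, so that observed imbalance does not decide the adjustment. Centre may be added but is optional, since randomisation was not stratified by it.

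The cost is a rewording of the Statistical analysis section, made before outcomes are compared by arm. No extra data or patients are needed.
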